##### Sample Size and Power

A power analysis based on an LMM indicates that a sample of 140 participants provides power of *β*=.84 to detect a moderate correlation (b=0.3) between LC-NE functioning and dispositional risks.

##### Experimental Design

Cross-sectional analysis of combined pupillometry, EEG, and behavioral and cognitive assessments.

##### Neurophysiological Measures

The validated pupillometric battery, as described in Objective 1, will be used to assess BPS and SEPR across multiple tasks. In a concurrent EEG, the ERP of ERN will be assessed using an age-appropriate Go/No-Go task [50]. Neurocognitive paradigms of irritability will be examined using a dot-probe task [95] and a frustrative reward learning task [96].

##### Cognitive Measure

To assess the verbal and cognitive abilities, we will conduct 2 subtests from the WPPSI [93].

##### Behavioral Measures

Temperament traits will be measured via caregiver reports with the Behavioral Inhibition Questionnaire (BIQ) [83] and Affective Reactivity Index (ARI) [84]. Negative emotionality will be assessed via Child Behavior Questionnaire-Very Short Form (CBQ-VSF) [85]. The 3 transdiagnostic factors of psychopathology will be assessed with the Child Behavior Checklist (CBCL 4‐18) [82].

##### Statistical Analysis Plan

We will apply LMM analysis with participants as random intercepts. These will allow us to explore associations between variables on a per-task level and control for potential covariates (age, gender, and IQ).

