#### Irritability

Irritability is a temperament trait of negative emotionality that is described by anger after frustration and attenuated fear under threat [45]. Irritability in children is the most pressing problem reported by help-seeking families [46]. Increased irritability predicted later conduct problems [47] and has been associated with a genetic risk for attention deficit hyperactivity disorder [48]. In contrast, irritability also predicted later internalizing [49]. This multifinality has been differentiated by error-related negativity (ERN) in EEG. In preschoolers with high irritability, increased ERN predicted later internalizing, while decreased ERN predicted later externalizing [50]. The ERN indicates an automated error detection that is modulated by LC-NE phasic activity [51]. Attenuated LC-NE phasic activity further attenuates a limbic fear response, which might promote externalizing behavior in irritable children [52]. We propose LC-NE phasic activity as an irritability correlate that differentiates between later externalizing and internalizing.

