#### Behavioral Inhibition

Behavioral inhibition is another temperament trait of negative emotionality that is described by wariness and avoidance. Behavioral inhibition in young children predicted later anxiety and internalizing psychopathology as adults [53]. Behavioral inhibition in children has also been associated with an increased ERN [54] and an increased neurophysiological reactivity to novelty [55]. It indicates elevated LC-NE phasic activity as an amplifier of the limbic fear response that emphasizes a general threat perception and promotes behavioral inhibition [56]. We will investigate patterns of LC-NE activity that correspond to the early dispositional risks of irritability and behavioral inhibition. We expect differentiating profiles of LC-NE functioning, where elevated LC-NE phasic activity predicts later internalizing and attenuated LC-NE phasic activity predicts later externalizing psychopathology.

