**Figure 3. F3:**
[figure not shown]
Work program of LOCUS-MENTAL with time flow, required personnel, and the associated tasks.

#### Objective 1

This study aims to validate a concise test battery assessing LC-NE system functioning in preschool children using pupillometric measures during passive tasks. The test battery will be evaluated for convergent and discriminant validity.

#### Objective 2

This study aims to associate LC-NE functioning with correlates of psychopathology in a cross-sectional study. Task 2.1 will determine whether LC-NE functioning profiles serve as markers of dispositional risks and differentiate between irritability and behavioral inhibition. Task 2.2 will examine whether LC-NE functioning further mediates the association between childhood adversity and transdiagnostic psychopathology.

#### Objective 3

This study aims to evaluate the prospective effect of LC-NE functioning in a developmental model of vulnerability and stress. Task 3.1 will investigate whether pupillometric measures of LC-NE functioning in preschool age predict risk for psychopathology at school age. Task 3.2 will assess LC-NE functioning as a mediator between early stress responses and later psychopathology.

#### Objective 4

This study aims to develop an objective tool of risk prediction in the preschool ages based on the pupillometric measures of LC-NE functioning. LC-NE function profiles in preschoolers define a normative development space, where individual deviations indicate quantitative risks for MHD.

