##### Expected Outcome and Study Hypotheses

Behavioral inhibition (BIQ score) is expected to correlate positively with both BPS and SEPR in the pupillometric battery of LC-NE functioning. In contrast, irritability (assessed via ARI score) is expected to show differential profiles of LC-NE functioning. We expect high irritability scores and high SEPR to be associated with higher internalizing symptoms, while high irritability scores and low SEPR will be associated with higher externalizing symptoms—these expected outcomes are supposed to match ERN profiles [101]. Furthermore, in the neurocognitive paradigms, participants with high-irritability-low-SEPR profiles are further expected to show increased attentional bias toward threat cues (threat perception) and decreased attentional shifts during frustration (frustrative reward learning). These patterns would suggest a subgroup with elevated risk for conduct disorders. We will further explore LC-NE functioning in children with both high irritability and high behavioral inhibition, who are expected to exhibit higher negative emotionality and an increased BPS as an index of an elevated LC-NE tonic activity.

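### Task 2.1 aims to differentiate irritability from behavioral inhibition, but nothing in its stated analysis separates the two traits or tests that they differ

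*Protocol article*

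**What the plan says.** Objective 2 states that Task 2.1 will "determine whether LC-NE functioning profiles serve as markers of dispositional risks and differentiate between irritability and behavioral inhibition". The Discussion repeats this aim.

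The Introduction puts both traits under one parent construct: "Irritability is a temperament trait of negative emotionality", and "Behavioral inhibition is another temperament trait of negative emotionality". Task 2.1, Behavioral Measures, has both rated by caregivers: "Temperament traits will be measured via caregiver reports with the Behavioral Inhibition Questionnaire (BIQ") and the ARI. Negative emotionality itself is measured with the CBQ-VSF.

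The Task 2.1 Statistical Analysis Plan is two sentences long. It says "We will apply LMM analysis with participants as random intercepts", and that the models explore associations task by task and "control for potential covariates (age, gender, and IQ"). It names no model with BIQ and ARI together, no adjustment for CBQ-VSF negative emotionality, and no comparison of the two traits.

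The hypotheses take a different form for each trait. For inhibition, "Behavioral inhibition (BIQ score) is expected to correlate positively with both BPS and SEPR in the pupillometric battery". For irritability, the prediction is a combination with SEPR: high irritability with high SEPR goes with internalizing, and high irritability with low SEPR goes with externalizing. Children high on both traits are to be explored.

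The power statement gives .84 for 140 children to detect b = 0.3 between LC-NE functioning and dispositional risks. It covers one association, not a difference between two. Attrition for this task is put at about 30%.

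**The concern.** A claim to "differentiate between irritability and behavioral inhibition" is comparative, and associations examined one trait at a time do not answer it. There are three ways to go wrong.

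- If the pupil index follows inhibition alone and the two scores correlate, ARI picks up part of the inhibition effect and looks like a marker in its own right.
- If the index follows what the traits share, chance can make one association significant and the other not. That looks trait-specific although the effects are equal.
- The protocol ties inhibition both to later internalizing (Introduction, Behavioral Inhibition) and to higher SEPR (Task 2.1 hypotheses). The predicted profile of high irritability, high SEPR and internalizing could therefore be inhibition showing through the ARI score, unless BIQ is held constant.

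At stake is whether a Task 2.1 result may be reported as specific to one trait.

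**Working it through.** **Inputs.** From the protocol: n = 140, effect 0.3, attrition about 30%, so 140 × 0.70 = 98. The protocol does not say whether 140 already allows for attrition, so both sizes are shown. Assumed: two-sided α = .05 and a BIQ-ARI correlation ρ of .30 to .49. These values correspond to loadings of .55 and .70 on a shared factor (.55² = .30, .70² = .49). The protocol gives no ρ. The calculations use one index value per child, not the full mixed model.

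**The plan's own figure.** A plain correlation of .3 gives power Φ(atanh(.3)·√(n−3) − 1.96).
- n = 140: Φ(3.62 − 1.96) = .95.
- n = 98: Φ(3.02 − 1.96) = .85.

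The stated .84 comes from a simulated mixed model whose variance inputs are not given, so it is neither confirmed nor refuted. The point does not depend on it.

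**Case 1: the index depends on BIQ only, r = .3.** The marginal correlation of ARI with the index is .3ρ. The probability that ARI is significant on its own is about Φ(atanh(.3ρ)·√(n−3) − 1.96).

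| n | ρ | .3ρ | Formula | Simulation |
|---|---|---|---|---|
| 140 | .30 | .090 | Φ(1.06 − 1.96) = .18 | about .19 |
| 140 | .49 | .147 | Φ(1.73 − 1.96) = .41 | about .42 |
| 98 | .30 | .090 | Φ(0.88 − 1.96) = .14 | about .14 |
| 98 | .49 | .147 | Φ(1.44 − 1.96) = .30 | about .29 |

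With BIQ in the same model, ARI is significant in about 4-6% of runs. The result depends on ρ: at n = 140 the single-trait rate is 11% at ρ = .2 and 57% at ρ = .6, and at ρ = 0 there is no inflation.

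**Case 2: the effect is common to both traits (simulation).** The share of studies in which exactly one trait is significant when each is tested alone:
- r = .3 with each trait: about 7-8% at n = 140, about 20% at n = 98.
- r = .17 with each trait (ρ = .30): about 40% at n = 140.

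The direct test of the BIQ coefficient minus the ARI coefficient rejects in about 5% of runs.

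**Mutual adjustment alone does not cure Case 2.** With both traits in one model and a common effect of r = .3, exactly one coefficient is significant in 26-64% of runs at n = 140 (ρ from .2 to .5). The difference itself has to be tested.

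**Power of that contrast if BIQ alone acts at .3.** The standard error is √[(1 − .3²)·2 / (n(1 − ρ))].
- n = 140, ρ = .30: √(1.82/98) = .136; .3/.136 = 2.20; power about .59.
- n = 140, ρ = .49: √(1.82/71.4) = .160; .3/.160 = 1.88; power about .47 (simulated .45 at ρ = .5).
- n = 98: simulated .44 at ρ = .30 and .33 at ρ = .5.

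**Precision cost of the joint model.** Variance inflation is 1/(1 − ρ²): 1/(1 − .09) = 1.10 and 1/(1 − .24) = 1.32.

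**The case against.** The strongest reply is that age, gender and IQ are nuisance covariates. BIQ and ARI are variables of interest, so their absence from that list does not show that they are fitted apart, and a condensed article may leave the predictor set to a fuller plan. This stands in part. A reader might infer that the protocol fits the traits in separate models or rules out a joint one. It says neither. What can be said is that the article has its own analysis section for this task, and nothing in that section delivers the comparison the aim requires.

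Second, the irritability hypothesis is not a parallel main effect. It is an irritability-by-SEPR pattern on CBCL outcomes, and the protocol never says that one significant and one non-significant trait would count as differentiation. This also stands. It means that a BIQ-minus-ARI contrast alone would not test the irritability prediction, so the remedy must also cover the interaction models. It does not remove the problem, because inhibition can produce the same profile there.

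Third, a substantial BIQ-ARI correlation is not a fact of the document. The shared parent construct and shared rater point towards one. The Introduction also describes attenuated fear in irritability and an amplified fear response in inhibition, which could lower it. The error rates are therefore conditional.

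Fourth, overlap is not ignored: the CBQ-VSF is collected and children high on both traits are explored. That describes the overlap without separating the traits.

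Finally, Task 2.1 is described as more optional, its models are said to explore, and it is not the primary outcome. This limits the weight of the point.

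**Conclusion.** The point holds in a limited form. Task 2.1 has a comparative aim, and the stated analysis contains neither a model that separates the two caregiver-rated traits nor a test of their difference. Inferring differentiation from per-trait associations would be unsound.

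The size depends on a correlation that the protocol does not give. Over the assumed .30 to .49, an inhibition-only effect at r = .3 is misread as an irritability association several times more often than the nominal 5%.

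It would go too far to say that a shared effect will often pass as trait-specific. At the protocol's own effect size of 0.3, a common effect usually makes both traits significant (about 90-92% of runs at n = 140). The 40% figure needs a weaker effect of about .17. The change is worth making, but it does not touch the core longitudinal objective.

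**What to change.** 1. In the Task 2.1 mixed models for BPS and SEPR, enter standardised BIQ and ARI together with age, gender and IQ. Rest any claim that an index differentiates the traits on the test of the BIQ coefficient minus the ARI coefficient, not on one being significant and the other not.
2. In the models of CBCL internalizing and externalizing on irritability-by-SEPR, add BIQ and BIQ-by-SEPR, so that the irritability profile is not inhibition under another name.
3. Report single-trait associations as secondary, and state the contrast's power: about .45-.59 at n = 140 and .33-.44 at n = 98 if inhibition alone acts at .3.

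The cost is analysis wording, since all scores are already to be collected. Single-trait coefficients lose some precision. The real trade-off is that the contrast is well short of the protocol's .80 target, so a non-significant difference must not be read as showing that the traits share one profile.

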##### Expected Outcome and Study Hypotheses

Behavioral inhibition (BIQ score) is expected to correlate positively with both BPS and SEPR in the pupillometric battery of LC-NE functioning. In contrast, irritability (assessed via ARI score) is expected to show differential profiles of LC-NE functioning. We expect high irritability scores and high SEPR to be associated with higher internalizing symptoms, while high irritability scores and low SEPR will be associated with higher externalizing symptoms—these expected outcomes are supposed to match ERN profiles [101]. Furthermore, in the neurocognitive paradigms, participants with high-irritability-low-SEPR profiles are further expected to show increased attentional bias toward threat cues (threat perception) and decreased attentional shifts during frustration (frustrative reward learning). These patterns would suggest a subgroup with elevated risk for conduct disorders. We will further explore LC-NE functioning in children with both high irritability and high behavioral inhibition, who are expected to exhibit higher negative emotionality and an increased BPS as an index of an elevated LC-NE tonic activity.

##### Risk Assessment, Participant Burden, and Ethical Considerations

This task is associated with the highest participant burden due to its combined EEG assessments and neurocognitive task demands. To mitigate this, we will provide additional breaks for the participants and offer food and drinks between assessments. We assume a higher attrition rate for this task compared to other tasks, estimated at approximately 30%. Thus, this task is designed as more optional, ensuring that potential dropouts will not compromise subsequent study objectives.

### Task 2.2: LC-NE Function Mediates the Association Between Childhood Adversity and Transdiagnostic Psychopathology

#### Participants

A sample of 300 preschool-aged children (aged 4‐6 years) will be recruited in accordance with the general recruitment strategy of the study.

#### Sample Size and Power

A power analysis based on a structural equation model indicates that a sample of 300 children provides a power of *β*=.80 to detect a moderate path coefficient (a=0.2) between latent variables of LC-NE functioning and psychopathology.

#### Experimental Design

Cross-sectional analysis of combined pupillometry, behavioral, and cognitive assessments will be used.

#### Neurophysiological Measures

The validated pupillometric battery, as described in Objective 1, will be used to assess BPS and SEPR across multiple tasks.

#### Cognitive Measure

To assess the verbal and cognitive abilities, we will conduct 2 subtests from the WPPSI [93].

#### Behavioral Measures

Transdiagnostic psychopathology factors (externalizing, internalizing, and p-factor) will be assessed with CBCL 4‐18. In addition, we will assess childhood adversity based on multiple sources. Specifically, a caregiver interview that captures adverse childhood experiences and other psychosocial domains (ACE+) [40], a respective child interview [86], validated child-report measures of adversity [88,89], and a report by the respective clinician from the outpatient clinic for those children recruited via the outpatient recruitment leg. This assessment approach will provide an index of cumulative adversity or will be differentiated into specific adversity domains.

#### Statistical Analysis Plan

Structural equation models will be applied to estimate the associations between the latent constructs (LC-NE functioning, transdiagnostic psychopathology, and childhood adversity). A best-fit path model will be used to reduce the complexity of the structural equation in the longitudinal study of Objective 3. A latent mediation model, in which LC-NE functioning is expected to mediate an association between previous childhood adversity and transdiagnostic psychopathology, will be applied. Independent models for BPS, SEPR, and each transdiagnostic factor will be estimated. Classification approaches will be applied in exploratory analyses to identify LC-NE function profiles in subgroups of psychopathology.

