## Methods

### Overview

LOCUS-MENTAL will achieve its objectives by combining pupillometric indices of LC-NE functioning and using a prospective panel study design (Figure 4). Pupillometry is assessed by video-based eye tracking during basic paradigms that are feasible in preschoolers. Transdiagnostic psychopathology is assessed by CBCL externalizing, internalizing, and total T-scores. Childhood adversity is assessed by interviewing caregivers, children, and clinicians. Pupillometric indices, transdiagnostic psychopathology, and childhood adversity are repeatedly measured in an accelerated longitudinal study: We assess preschoolers (aged 4‐6 years) in an initial assessment with reassessments after one year (aged 5‐7 years) and after 2 years (aged 6‐8 years). This accelerated design allows revealing causative effects of LC-NE functioning on psychopathology from 4 to 8 years of age. In addition, this allows quantifying LC-NE functioning as a mediator in the effect of childhood adversity on psychopathology. In distinct subtasks, LC-NE functioning is elaborated as a neurophysiological mechanism of established dispositional risks, while LC-NE functioning in stress regulation is explored by combined pupillometry and analysis of hair cortisol levels and salivary cortisol after a social stress test. This will characterize LC-NE functioning profiles in the interaction of dispositional risk and stress. Finally, LOCUS-MENTAL applies normative modeling on the pupillometric data to develop a tool for risk prediction of developmental trajectories in transdiagnostic psychopathology. An overview of all measures is provided below (Table 1). The reporting of this study protocol follows the STROBE (Strengthening the Reporting of Observational Studies in Epidemiology) guidelines for longitudinal cohort studies [81]. The completed checklist is available in Checklist 1.

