#### Expected Outcome and Study Hypotheses

We hypothesize associations between retrospective childhood adversity, LC-NE function, and transdiagnostic psychopathology. For example, lower LC-NE tonic activity is expected to represent a resilience to the negative impact of childhood adversity on psychopathology. In addition, we expect profiles of LC-NE functioning that are associated with patterns of transdiagnostic psychopathology; BPS is expected to positively correlate with the p-factor, whereas increased and decreased SEPR are expected to positively correlate with internalizing and externalizing symptoms, respectively.

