##### Behavioral Measures

At each timepoint assessment of the behavioral measures, as described in Task 2.2, will include caregiver questionnaires (CBCL 4‐18) and the multiple-source assessment of childhood adversity (see Table 1).

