##### Expected Outcome and Study Hypotheses

This core of LOCUS-MENTAL will be informed by the outcome of task 2.2. We expect (see Figure 1) that higher BPS as an index of LC-NE tonic activity predicts a higher p-factor. Increased and decreased SEPR as an index of LC-NE phasic activity is expected to predict higher internalizing and externalizing symptoms, respectively. This would predict future psychopathology based on pupillometric markers. The stability of the investigated constructs is controlled for by autoregressive effects. The structural equation models will be explored for the covariate effects of childhood adversity, previous psychopathology, and received clinical support (eg, in the context of the outpatient clinic for early detection).

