## Discussion

### Principal Findings

The LOCUS-MENTAL protocol outlines a longitudinal study design with the primary aim to establish LC-NE functioning as a neurobiological predictor of later psychopathology in childhood. We anticipate that the validation phase (Objective 1) will demonstrate convergent and discriminant validity of the pupillometric markers BPS and SEPR with sufficient reliability. By developing and validating a child-friendly, pupillometry-based tool, this aims to bridge a critical gap between neurobiological mechanism and clinical risk prediction, which is based solely on behavioral observation. Accordingly, this is a prerequisite to ensure the method sensitivity and specificity. This would provide a concise test battery that assesses a neurobiological mechanism that could be implemented in future clinical studies capturing a potential biomarker of psychopathology in early childhood. Furthermore, we hypothesize that BPS and SEPR will cross-sectionally differentiate between transdiagnostic risk profiles, such as irritability and behavioral inhibition, and serve as a mediator between childhood adversity and psychopathology (Objective 2). This would provide an underlying neurobiological basis for temperament dimensions that are also based on caregiver reports. In the longitudinal data, as a core outcome, we expect to reveal baseline LC-NE functioning at age 4‐6 years to predict the development of psychopathology at school age (Objective 3). This central component of the LOCUS-MENTAL project would provide causative evidence for an impact of LC-NE functioning on transdiagnostic mental health conditions. These findings will be used in forming a normative model as a pupillometry-based risk prediction tool, establishing a key neurobiological susceptibility mechanism that mediates the impact of early adversity on psychopathology (Objective 4). This will allow a translation of the experimental findings to clinical practice. For example, children associated with an elevated risk for psychopathology based on LC-NE functioning could be supported by evidence-based treatments that are effective before the onset of a mental health condition. This would emphasize a targeted prevention approach. We conclude that the identification of a neurobiologically grounded risk marker could transform our mental health infrastructure from interventions that are applied years after the onset of mental health problems to early and targeted support. Ultimately, this aims to reduce the lifetime burden of mental health problems.

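### A longitudinal adversity–LC-NE–psychopathology mediation is announced, but the only one specified at task level takes mediator and outcome from the same visit, so a reverse effect could be reported as mediation

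*Protocol article*

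**What the plan says.** **Task 2.2.** Its title says that LC-NE function mediates the association of childhood adversity with psychopathology. Its Experimental Design reads "Cross-sectional analysis of combined pupillometry, behavioral, and cognitive assessments will be used". Its Statistical Analysis Plan specifies "A latent mediation model, in which LC-NE functioning is expected to mediate an association between previous childhood adversity and transdiagnostic psychopathology", with separate models for BPS, SEPR and each psychopathology factor. The hypotheses are worded more cautiously: "We hypothesize associations between retrospective childhood adversity, LC-NE function, and transdiagnostic psychopathology".

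**What is announced for the longitudinal data.** The Methods Overview states "Pupillometric indices, transdiagnostic psychopathology, and childhood adversity are repeatedly measured in an accelerated longitudinal study" and, after describing the accelerated design, "In addition, this allows quantifying LC-NE functioning as a mediator in the effect of childhood adversity on psychopathology". The abstract likewise says that cross-lagged panel models will quantify causal effects among LC-NE functioning, adversity and psychopathology.

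**What Task 3.1 specifies.** The cross-lagged model runs from previous LC-NE functioning to later CBCL factors. Adversity appears only here: "The structural equation models will be explored for the covariate effects of childhood adversity, previous psychopathology, and received clinical support". The data for more are scheduled: pupillometry at each time point, and behavioral measures at each time point that "will include caregiver questionnaires (CBCL 4‐18) and the multiple-source assessment of childhood adversity".

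**Task 3.2.** Its mediation of psychopathology takes the cortisol stress response as exposure, not adversity. Its adversity analysis has the stress response as its endpoint.

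**The anticipated conclusion.** Principal Findings expects to establish a "mechanism that mediates the impact of early adversity on psychopathology".

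**The concern.** Adversity is retrospective, so the exposure plausibly comes first. The step that makes LC-NE a mediator, its effect on psychopathology, has no time order when both are taken at T1. If a child's symptoms shift pupillometric arousal, adversity, LC-NE and CBCL will correlate in the pattern that the mediation model looks for, with LC-NE doing nothing.

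The article's general sections and its task sections also disagree. The former promise that the three-wave data will address the adversity mediation. The latter place it at one visit and leave adversity as an exploratory covariate in the longitudinal model. A covariate term is not an indirect path. At stake is one of the study's headline statements, that LC-NE functioning mediates the impact of early adversity.

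**Working it through.** **1. The plan's own figure.** Task 2.2 states power 0.80 for one path of 0.2 between latent LC-NE functioning and psychopathology, n=300. For an observed correlation of 0.2, two-sided 0.05: atanh(0.2)·√297 − 1.96 = 3.49 − 1.96 = 1.53, so power is 0.94. Power of 0.80 corresponds to a correlation of about 0.161 = 0.2 × 0.81, which is plausible for latent variables with imperfect indicators. Loadings and alpha are not given, so the figure can be neither confirmed nor refuted, and this point does not depend on it. The path powered is the one whose direction is in doubt, not the indirect effect.

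**2. Why fit cannot settle direction.** Three constructs have three covariances. A mediation model that keeps the direct path uses three paths, so its structural part is saturated. Reversing the arrow between LC-NE and psychopathology gives the same fit.

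**3. A reverse-only case by hand.** Assume adversity→symptoms 0.3, symptoms→LC-NE 0.3, and no effect of LC-NE on symptoms (standardized, n=300).
- First path, adversity to LC-NE: 0.3 × 0.3 = 0.09. SE = √((1 − 0.0081)/298) = 0.0577, z = 1.56, chance of p<.05 about 0.34.
- Second path, LC-NE to symptoms given adversity: (0.3 − 0.09 × 0.3)/(1 − 0.0081) = 0.275. SE about 0.053, z about 5.2, chance of p<.05 above 0.99.
- Both significant: about 0.34. Spurious indirect effect: 0.09 × 0.275 = 0.025.

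Simulation of this case gave 33% and 0.024. Over adversity–symptom paths of 0.2 to 0.5 and symptom–LC-NE paths of 0.2 to 0.4, the rate ran from 10% to 93%.

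**4. A three-wave version.** Assumed: stability 0.6 for both constructs, adversity affecting both, no effect of LC-NE on psychopathology, n=300. Implied correlations are about 0.30–0.35 (adversity–LC-NE), 0.32 (adversity–psychopathology) and 0.18–0.27 (LC-NE–psychopathology). Mediation is declared when both paths have p<.05.

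| Reverse effect per wave | T1-only model declares mediation |
|---|---|
| 0 | at most 6% |
| 0.10 | about 35% |
| 0.15 | about 64% |
| 0.20 | about 88% |

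Without a direct adversity effect on LC-NE, the rate for reverse effects of this kind was still 12% to 84%.

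**5. Two ways of putting the mediator before the outcome.** Power was simulated under true mediation (stability 0.6 with LC-NE→CBCL 0.2, or 0.75 with 0.15), with full data and with the 73.5% retention cited in the Task 3.1 risk assessment (300 × 0.735 ≈ 220 children).

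| Model | False positives, reverse-only truth | Power, adversity acted before T1 | Power, adversity acts at every wave |
|---|---|---|---|
| Adversity → T1 LC-NE → later CBCL, adjusted for T1 CBCL and adversity | near 5% | about 87–99% | about 87–99% |
| T1 adversity → T2 LC-NE (given T1 LC-NE, CBCL) → T3 CBCL (given T2 CBCL, adversity) | about 2% or less | about 3–6% | about 28–70% |

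The second model has almost no power in the middle column because adjusting T2 LC-NE for T1 LC-NE removes whatever adversity had already done to LC-NE by T1.

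**The case against.** **Longitudinal intent is stated.** A reader might infer that the adversity mediation is confined to one visit and that the follow-up data go unused for it. The documents do not support that. The abstract and the Overview announce longitudinal estimation with adversity, Task 2.2 says that a best-fit path model will simplify the Objective 3 equation, and Task 3.1 says that it is informed by Task 2.2. This is a condensed article and a separate analysis plan may exist. What stands is that the announced model is not written at task level, and that the task text which does exist gives adversity a different role.

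**The disputed arrow is tested elsewhere.** Task 3.1 tests LC-NE to later CBCL with autoregressive control in the same 300 children. Under a reverse-only truth, that type of lagged path was significant in only about 4% to 7% of simulated studies. This protects the single path, but no indirect effect from adversity is specified there. Figure 6 is not shown, so whether the reverse path is fitted cannot be determined.

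**The wording is partly associational.** The Task 2.2 hypotheses speak of associations, and the sentence in Principal Findings is tied to Objective 4 and follows the longitudinal results. It is therefore too strong to say that a reverse effect would be reported as mediation. It could be.

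**The rates rest on assumed inputs.** The only stability figures given are BPS correlations of 0.69–0.81 in 26 children; SEPR is said to be lower. The 10% to 93% range includes modest bias. This stands as a limit on the size, not on the direction.

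**Conclusion.** The concern holds as an inconsistency with a consequence for inference. The general sections promise a longitudinal adversity mediation, while the only one specified takes LC-NE and CBCL from the same visit and cannot order them. If symptoms affect LC-NE functioning, that model could show mediation that is not there: about 35% to 88% of studies for reverse effects of 0.10 to 0.20 at stability 0.6, and at most 6% with no reverse effect. Stability, reverse effects and adversity effects are all assumptions.

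A reader might also infer that the strictest ordering, T1 adversity to T2 LC-NE to T3 CBCL, should be the sole test. Task 2.2 asks about adversity that has already occurred, and for that this model has almost no power.

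Severity: should-fix. The primary aim, prediction of psychopathology by LC-NE functioning, has its own longitudinal test in Task 3.1.

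**What to change.** - In Task 3.1, specify the adversity indirect effect with the mediator measured before the outcome: retrospective adversity reported at T1, to T1 LC-NE, to T2/T3 CBCL, adjusting for T1 CBCL and adversity and including the cross-lags from psychopathology to LC-NE.
- Report T1 adversity to T2 LC-NE to T3 CBCL, with prior-level adjustment, as a supplementary analysis of ongoing adversity only.
- Label the Task 2.2 model as associational, and align the abstract, the Overview, the Task 2.2 title and analysis section, and Principal Findings with that.

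The cost is one more model on data already scheduled. The estimate depends on follow-up retention, and the path from adversity to T1 LC-NE remains retrospective, so the result still rests on reported past adversity. The longitudinal study was scheduled to start in April 2026, so the change can be made before any follow-up data exist.
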